### Sample size

As this is a pilot study, power-based sample size calculations have not been conducted. It is anticipated that findings from this study will inform sample size and power calculations for a subsequent definitive randomised controlled trial (RCT). The proposed sample size of 30 participants per study arm, a total of 60 participants, is based on recommended sample sizes for pilot studies preceding a main trial powered to detect a small to medium effect size (i.e. 0.1–0.3) [29] and is consistent with the median intended sample size of 30 participants per arm in registered pilot and feasibility trials [30]. Moreover, this sample size is sufficient to estimate recruitment and attrition rates ahead of a larger RCT across multiple sites. While there are no previous studies using a similar 12-week protocol among a wholly inpatient population to guide estimates of attrition, based on the attrition rates of studies among outpatient and non-psychiatric samples (7–19%) [11, 17, 18], we have conservatively allowed for a 20% attrition rate when considering our intended sample size.

### Recruitment strategy

As the number of potential participants at each unit will be limited to the number of beds in the ward, a rolling recruitment strategy (i.e. ongoing recruitment over the study period) will be employed. This strategy will create ongoing recruitment opportunities due to patient flow through the units and help minimise the effects of attrition on the planned sample size. Recruitment and retention will be monitored at regular intervals (i.e. weekly), with recruitment projections revised accordingly.

### Data collection

Baseline and post-intervention interviews will assess all primary and secondary outcomes, with the exception of intervention feasibility and acceptability which will be assessed on completion or discontinuation of the intervention, and are expected to take 60 min to complete. Mid-intervention interviews will measure self-reported levels of physical activity and symptoms of depression, anxiety and stress over the preceding week and are expected to take 20 min to complete. All interviews will be conducted by trained research staff, with the clinical assessments conducted by a research nurse.

#### Baseline assessment

Consenting eligible participants in both the intervention and control groups will complete a structured baseline interview administered by one of the research team. The baseline interview will collect information on demographic characteristics (age, gender, ethnicity, level of education, employment prior to incarceration, marital status), incarceration history (as a juvenile and adult), perceived general health status, psychiatric history as indicated by diagnosed mental health disorders (including substance use disorders), and previous exergaming experience (intervention group only). It will also will include the administration of validated instruments to assess potential effectiveness outcomes related to participants’ physical and mental health and a clinical assessment of cardiovascular and metabolic risk.

#### Primary outcome measures

##### Study feasibility

Feasibility will be measured by the number of participants recruited to the study; participation refusal rates; participant compliance and adherence (i.e. number, length and frequency of intervention sessions attended; compliance with wearing an accelerometer); rates of retention/attrition; occurrence of adverse events (e.g. injury, event related to psychotropic medication, abnormal increase in heart rate during intervention); fidelity of intervention delivery.

Recruitment data will be recorded in screening and enrolment logs, consent forms and study records. Data on intervention compliance, adherence, safety and fidelity of delivery will be recorded on a weekly basis.

In cases where enrolled participants discontinue before completion of the intervention period, reasons for early withdrawal will be documented. Participant discontinuation of the programme due to discharge from the unit will also be documented.

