#### Other measures

##### Exercise intensity

Perceived exertion during exergaming sessions will be measured using the OMNI-Walk/Run Scale of Perceived Exertion assessment for adults [26]. Using the OMNI walking/running pictorial as a visual aid, participants will be asked to rate how hard or easy they perceive the exergaming session to be, based on their perceived levels of exertion. The OMNI-Walk/Run Scale includes numerical categories from 0 to 10, representing a range of exertion levels from “extremely easy” (0) to “extremely hard” (10). OMNI ratings of perceived exertion (RPE) have been validated against objective physiological measures of exercise intensity [26].

In order to ensure that participants do not exceed 85% of their maximum heart rate, as determined using an age-based formula (220−age of participant × 0.85), heart rate monitoring will be conducted at 1-min intervals during the baseline and post-intervention step tests and 10-min intervals during each exergaming session. If, at any time during the step tests, a participant’s heart rate approaches 85% of their maximum heart rate, the test will be discontinued. If this occurs during an exergaming session, a lower intensity game will be used for the remainder of the session.

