#### Quantitative data

Quantitative feasibility outcomes will be reported descriptively and narratively. Rates of recruitment, retention, protocol adherence/compliance, intervention fidelity and adverse events will be presented as frequencies and proportions. Participants recruited to the study in the initial wave (January–March 2020), prior to the suspension of recruitment during the COVID-19 outbreak in NSW (March–June 2020), will be replaced by new participants to achieve the target sample size and will have their data excluded from the final analysis.

Primary and secondary outcomes will be analysed descriptively and presented for the overall sample and by group. Means, standard deviations and ranges, or medians and interquartile ranges, as appropriate, will be reported for continuous data, and frequency counts and proportions for categorical data, with associated 95% confidence intervals. Missing data for each of the primary and secondary outcome measures will be described using descriptive statistics. Missing data will not be replaced or imputed.

As this pilot study primarily aims to determine the feasibility of conducting a future definitive intervention trial and is not powered for statistical hypothesis testing, statistical analysis of the potential effectiveness of the intervention will not be performed on the clinical outcome data. Physical activity, cardiorespiratory fitness, and cardiometabolic risk data collected at each timepoint will be summarised descriptively for each group. Whilst between-group statistical comparisons will not be undertaken, post-intervention differences between groups will be reported using estimated mean differences and 95% confidence intervals, where appropriate.

Perceptions of exercise intensity, general health status and the study experience will be reported descriptively and narratively. All analyses will be performed using IBM SPSS software (Version 27) [40].

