#### Safety monitoring and reporting

Safety monitoring and reporting procedures will be aligned with the requirements for clinical trials conducted in Australia [44] and in NSW Public Health Organisations in particular (*Office for Health and Medical Research Policy Directive PD2017_039-Safety Monitoring and Reporting for Clinical Trials Conducted in NSW Public Health Organisations*).

The occurrence of any unexpected or adverse events during the study period, irrespective of whether they may be causally related to the study, will be recorded. Daily monitoring of adverse events will be conducted via brief interviews with staff and patients and health record review. An adverse event that meets the criteria for a serious adverse event (SAE) will be reported to all relevant ethics committees: JHFMHN Human Research Ethics Committee (HREC), Aboriginal Health & Medical Research Council (AH&MRC). SAEs occurring after a subject has withdrawn from, or completed participation in, the study will not be reported unless the investigators believe that the event may have been caused by the study intervention or a protocol procedure. Investigators will determine potential causality based on whether there is a temporal relationship to participation in the study, as well as whether the event is unexpected or unexplained given the participant’s previous medical conditions and current medications.

Prior to each exergaming session, the Dynamic Appraisal of Situational Aggression (DASA) will be completed for each participant. The DASA is an instrument designed to assess the risk of imminent violence (i.e. within 24 h of administration) in psychiatric patient populations [45]. Any participant that presents a risk of aggression/violence will be excluded from the session for that day and will recommence sessions subject to re-appraisal of risk.

In cases where a participant discloses, or research staff are alerted to, a new and/or unmanaged health condition during the course of the study, a referral form will be completed and handed over to clinical staff at the study site for appropriate follow-up. Information alerting participants to this referral process is included in the PIS.

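### Adverse events are sought more intensively in the exergaming arm, so a single by-group adverse-event proportion would not compare like with like

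*Protocol article*

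**What the plan says.** **What counts.** Under Study feasibility, the measures include "occurrence of adverse events (e.g. injury, event related to psychotropic medication, abnormal increase in heart rate during intervention". The list is open, and only its last example, "abnormal increase in heart rate during intervention", is tied to the intervention. The first primary outcome is "intervention feasibility and acceptability" (Outcomes; Data collection).

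**How it is reported.** Under Quantitative data, "intervention fidelity and adverse events will be presented as frequencies and proportions". The next paragraph adds: "Primary and secondary outcomes will be analysed descriptively and presented for the overall sample and by group".

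**How events are found in both arms.** Under Safety monitoring and reporting, "Daily monitoring of adverse events will be conducted via brief interviews with staff and patients and health record review". Events are recorded whatever their cause. Table 1 marks the adverse-event check for weeks 1 to 12 in a column that covers exergaming and usual care, without the intervention-only asterisk.

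**What only the exergaming arm has.** All sessions are supervised face to face, and the supervising researcher writes down the heart rate that each participant reads from the tracker (Interventions, Exergaming). Exercise intensity presents these readings, at "10-min intervals during each exergaming session", as a safety check. Its other heart-rate safety check is at the baseline and post-intervention step tests, which Table 1 does not restrict to one arm.

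**The concern.** Two groups' adverse-event proportions can be set side by side only if events had a similar chance of being noticed and recorded in each. Here the exergaming arm has the shared daily check plus a second route: direct observation and repeated heart-rate readings during sessions. One of the named adverse events fits that second route closely and has no stated counterpart in usual care.

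If the results show one proportion per arm, a reader cannot tell whether a higher exergaming figure reflects harm from the sessions, closer watching, or both. The study is meant to inform a randomised trial, so its descriptive safety picture will be carried forward. If the detection route is not noted when an event is logged, it is unlikely to be recoverable later.

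**Working it through.** The article states no adverse-event rate or detection rate, so there is no figure of its own to reproduce. The check has three parts.

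**1. Extra surveillance, from the stated schedule**
- Sessions: 3 per week × 12 weeks = 36 per participant at full attendance.
- Gaming time: 36 × 30 min = 18 h. With the 10-min warm-up and 5-min cool-down it is 36 × 45 min = 27 h.
- In-session readings: 30 min at 10-min intervals gives about 3 per session, so 36 × 3 = about 108 per participant. Controls have no sessions and so no equivalent.

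**2. Is there a matching route in controls?**
- The daily interview and record review apply to both arms, so injuries and medication-related events can be found in either.
- Trackers are worn in both arms for 14 weeks and log heart rate every minute (Potential effectiveness of intervention). The article describes this as physical-activity data, returned to participants as a weekly summary with average heart rate. It does not say that anyone reviews it for safety, and it gives no rule for calling a control reading an adverse event.
- The in-session reading comes from the same tracker. The arms therefore differ in whether a reading is looked at and recorded at the time, not in the device.

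**3. How far could a by-group figure move? (assumed rates, for illustration only)**

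*Pure detection difference.* Let p be the true proportion with an event in both arms and d the control arm's detection relative to exergaming. Spurious excess = p × (1 − d).
- p = 10%, d = 0.9: 1 point.
- p = 20%, d = 0.7: 6 points, that is 6.0 against 4.2 participants of 30. The 95% half-width is 1.96 × √(0.20 × 0.80/30 + 0.14 × 0.86/30) = about 19 points.
- p = 30%, d = 0.5: 15 points.
- d = 1: 0 points.

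*Added session-detected events.* Suppose 20% in each arm have an event found by the common check, and a further proportion q of exergaming participants independently have a session-detected event. The exergaming proportion is 1 − 0.80 × (1 − q).
- q = 5%: 24%.
- q = 10%: 28%.
- q = 20%: 36%.

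The control figure stays at 20%. This excess of 4, 8 or 16 points cannot be split into real harm and detection without knowing the source of each event.

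With 30 per arm, one extra participant with an event moves a proportion by 1/30 = 3.3 points, and two by 6.7 points.

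**The case against.** **Heart rate is measured in both arms.** A reader might infer that heart-rate events can be detected only under exergaming. The article does not support that: trackers log heart rate every minute in both groups, and step-test monitoring is not arm-specific. What stands is narrower. No stated procedure turns control tracker data into adverse events.

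**"abnormal increase in heart rate during intervention" may refer to the study period.** Table 1 labels weeks 1 to 12 as intervention for exergaming and usual care alike, so the event need not be impossible in controls. That reading is open, but the control arm would then need a matching definition, and none is given.

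**Session events are real harms.** A reader might infer that any exergaming excess is detection bias. That is wrong. An injury or heart-rate event provoked by a session is a consequence of the programme and belongs in its count. Only over-detection of background events is bias, and it could be zero if the shared daily check finds events equally well in both arms.

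**By-group reporting is inferred.** The adverse-event sentence does not mention groups, and some items beside it, such as fidelity, have no obvious control column. The inference is still the natural one, because adverse events sit within a primary outcome and no exception is made.

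**The aggression rating adds to detection.** A reader might infer this from "Prior to each exergaming session, the Dynamic Appraisal of Situational Aggression (DASA) will be completed for each participant". The rating assesses the risk of imminent violence and governs entry to a session. It does not detect adverse events and adds nothing to this point.

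**Little depends on it, and layout belongs in the analysis plan.** No between-group test is planned, Table 2 has no adverse-event criterion, and the article already acknowledges possible bias from the non-randomised, unblinded design. This limits the consequence. Table layout can indeed wait for the analysis plan, but detection source has to be captured during data collection.

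**Conclusion.** The point holds in a limited form. Ascertainment is more intensive in the exergaming arm, by 36 supervised sessions and about 108 heart-rate readings per participant at full attendance. The heart-rate event has no stated control-arm definition. A single by-group adverse-event proportion would therefore not be like for like.

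Part of any excess could be genuine session-related harm and part extra detection. The article fixes the size of neither. The 0 to 15 point range for a pure detection difference, and the 4 to 16 points for added session-detected events, rest wholly on assumed rates.

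The conclusion assumes that the by-group sentence covers adverse events as part of feasibility, and that tracker data are not screened for adverse events in controls. The effect is confined to interpreting the descriptive safety results. It does not reach a hypothesis test or a progression criterion.

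**What to change.** 1. Add a field to the adverse-event form for detection source: common daily check, exergaming session, step test or other. Allow more than one source, because a session injury may also surface in the daily interview.
2. Under Quantitative data, keep all events in the exergaming arm's total, and add a by-group presentation restricted to events found by the common daily check.
3. Show session-detected events, including the heart-rate event, on a separate exergaming-only line, per participant and per session, with no control column.
4. Under Study feasibility, either label the heart-rate event as exergaming-only or define it identically in both arms from the tracker data.

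The cost is one form field and one extra table, with no added visits or procedures. The drawback is that readers have two adverse-event tables to read together. Keeping the full exergaming total ensures that the restricted presentation does not hide real session-related harm.

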##### Acceptability of intervention

**Acceptability of intervention to participant:** Participant acceptability of the exergaming intervention will be assessed via post-intervention evaluation surveys (approximately 5 min) administered by research staff. Acceptability questions have been adapted from Kimhy et al. [17] and include questions on self-reported satisfaction with the intervention, ease of use of the exergaming system, and motivation to use exergaming as a form of physical activity in the future. Perceived utility of the intervention will be measured by asking participants about the impact of exergaming on their physical and mental health.

**Acceptability of intervention to staff at the study sites:** Acceptability of the exergaming intervention from the service perspective will be assessed via a post-intervention evaluation survey (approximately 5 min) using questions based on the theoretical framework of acceptability proposed by Sekhon et al. [31]. Areas assessed include staff perceptions of the intervention content and delivery, benefit for patients, and barriers to implementation and uptake.

##### Potential effectiveness of intervention

The potential effectiveness of the exergaming intervention will be assessed by measuring baseline to post-intervention changes in physical health outcomes:

i.Levels of physical activityii.Cardiorespiratory fitnessiii.Measures of cardiometabolic risk

**Physical activity: **Subjective levels of physical activity in the preceding week will be measured at baseline, mid-intervention and post-intervention using the Simple Physical Activity Questionnaire (SIMPAQ), a 5-item tool designed to assess physical activity and sedentary behaviour among people with mental illness [32]. The SIMPAQ measures self-reported activity over the previous week, including time spent in bed, sedentary time, structured exercise participation, and incidental or non-structured physical activity. In a validation study across 23 countries, the SIMPAQ was administered in a diverse sample of psychiatric patients, in both inpatient and outpatient settings, and found to be a reliable and valid tool for the assessment of self-reported physical activity [32].

Objective measures of daily physical activity during the study period will be obtained via accelerometry data. Following the baseline interview, all participants in both the intervention and comparison groups will be issued with an wrist-worn activity tracker (Fitbit® Charge 3) which they will be asked to wear the for the duration of the intervention period and up until the post-intervention assessments, totalling 14 weeks of activity monitoring. The Fitbits will only be worn whilst participants are out of their cell/room and participants will be required to check them in and out each day. Accelerometry data, obtained at 1-min intervals, will include number of steps taken, heart rate, energy (i.e. kilojoule) expenditure, and physical activity intensity as indicated by metabolic equivalent of task (METs) thresholds [33]. All participants will be provided with a weekly summary of their progress which will include their average steps over the preceding week, average heart rate, activity intensity levels (i.e. low, average, high) and average energy expenditure.

**Cardiorespiratory fitness:** Cardiorespiratory fitness at baseline and post-intervention will be determined via submaximal exercise testing using a modified version of the YMCA 3-min Step Test [34]. The modified YMCA step test protocol, which measures post-exercise heart rate recovery, has been shown to be a valid method of estimating VO_2_max [34–36], a measure of maximal oxygen consumption during exercise, with higher values of VO_2_max indicating higher levels of cardiorespiratory fitness.

**Cardiometabolic risk:** A clinical assessment of cardiovascular and metabolic risk factors, using the APSS (stage 3), will be conducted at baseline and post-intervention. Stage 3 of the APSS Tool obtains measurements of cardiovascular and metabolic risk factors (i.e. anthropometry, resting blood pressure, blood measures). This will entail measuring participants’ weight, BMI, waist circumference, hip circumference, and resting blood pressure. Blood samples will be obtained for testing of lipid profiles (total cholesterol, high-density lipoprotein (HDL), low-density lipoprotein (LDL), triglycerides), blood glucose levels (HBA1c, fasting glucose), and liver function. Capillary blood samples for lipid and glucose testing will be collected via fingerprick and analysed through a point-of-care testing machine. Blood for liver function testing will be collected via venous sampling.

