**Methods:**

This non-randomised, two-arm pilot study will employ a pre-test/post-test parallel group design, comparing the exergaming intervention with a “routine treatment” control. Two high-secure, sub-acute wards in the Long Bay Hospital Mental Health Unit will be non-randomly allocated to either the exergaming intervention or the “routine treatment” control group.

The intervention group will receive a 12-week programme comprising three 30-min exergaming sessions per week using various Xbox Kinect^TM^ activity-based games designed to simulate moderate intensity exercise. The “routine treatment” group will continue to receive the standard model of care delivered by the Justice Health and Forensic Mental Health Network. Accelerometers will be distributed to all participants to collect daily energy expenditure, number of steps taken, intensity of physical activity and heart rate data throughout the study.

The primary outcomes are (1) intervention feasibility and acceptability, and (2) baseline to post-intervention changes in physical health outcomes (levels of physical activity; cardiovascular fitness; clinical measures of cardiometabolic risk). Secondary outcomes are baseline to post-intervention changes in mental health outcomes (depression, anxiety, stress, positive psychiatric symptoms). Outcomes will be assessed at baseline, mid-intervention, and post-intervention.

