### Study aims and objectives

This pilot study aims to investigate the feasibility, acceptability and potential effectiveness of a novel intervention (exergaming) to promote physical activity among patients of a secure mental health unit. The results will inform the design and methodology of a subsequent randomised controlled effectiveness trial.

The specific objectives of the study are to:Determine whether the pilot exergaming programme (FIT HEART) is a feasible intervention for improving physical activity levels among patients in a secure mental health unit, as measured by recruitment rates, retention in the programme, protocol adherence, and patient and staff acceptability ratings.Assess whether participants who receive the FIT HEART programme demonstrate greater improvements in physical activity levels and clinical physical health measures (anthropometry; blood parameters; blood pressure), compared to those who receive routine treatment only.

Based on the emerging evidence, it is hypothesised that the FIT HEART programme exergaming will be a feasible and acceptable form of physical activity intervention among this patient group. Findings on the potential effectiveness of the intervention as an adjunct to routine care in providing physical and mental health benefits to patients will inform hypotheses for a future randomised trial.

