#### Routine treatment

Enrolled participants on the control unit will receive “routine treatment”, defined as the standard model of care provided by JHFMHN (i.e. usual care). Structured physical activity (e.g. organised walking, gym sessions) over the 14 weeks of monitoring that occurs outside of the assessment periods will be recorded.

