##### Study participation experience

All participants will be asked about their experience of participation in the study. Specifically, they will be asked whether they enjoyed being part of this study; whether they found wearing the Fitbit comfortable/uncomfortable; if they spent less time sitting while wearing the Fitbit; whether their usual daily routine had changed since being part of the study; if the weekly progress Fitbit information they were provided was useful; and, what things they liked most and least about the study. They will also be given the opportunity to provide comments or suggestions about the project.

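### The control arm is described as routine treatment only, but it also receives an activity tracker and weekly activity feedback, so the contrast is exergaming added to tracker feedback

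*Protocol article*

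**What the plan says.** Under Study aims and objectives, the second objective asks whether FIT HEART participants improve more in physical activity and clinical measures "compared to those who receive routine treatment only". Under Routine treatment, the control condition is "defined as the standard model of care provided by JHFMHN (i.e. usual care", with no mention of a tracker or of feedback.

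Under Potential effectiveness of intervention, "all participants in both the intervention and comparison groups will be issued with an wrist-worn activity tracker". It is worn "up until the post-intervention assessments, totalling 14 weeks of activity monitoring", out of cell only, and "participants will be required to check them in and out each day". The same section adds: "All participants will be provided with a weekly summary of their progress which will include their average steps over the preceding week". The summary also covers heart rate, energy expenditure and an activity level graded low, average or high. The Exergaming section shows that the device displays heart rate to the wearer.

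The abstract's Methods paragraph says that accelerometers go to everyone, but presents this as data collection and does not mention the summaries. It lists among the primary outcomes "baseline to post-intervention changes in physical health outcomes (levels of physical activity". Under Study participation experience, all participants are asked, among other things, "if they spent less time sitting while wearing the Fitbit", whether their daily routine changed, and whether the weekly information was useful.

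**The concern.** A tracker that patients can read, together with a weekly graded summary, is self-monitoring with feedback. Collecting accelerometry does not require returning it to patients each week, so this goes beyond measurement. Nothing in the article says that usual care on these wards includes it. The objective and the control definition therefore name one comparator while the data collection section delivers another, and the component in question acts on physical activity, a listed primary outcome.

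At stake is what the between-group results can be said to show. The Quantitative data section plans post-intervention mean differences with 95% confidence intervals. The aims and Sample size sections say that the pilot will inform the design, hypotheses and sample size of a later randomised trial. A reader who takes the comparator from the objective would treat the difference, and the control-arm changes and SDs, as describing routine care. Strengths and limitations covers non-random allocation, confounding, contamination by the intervention and lack of blinding, but not this shared exposure.

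**Working it through.** The plan states no figure on this point, so there is none to reproduce. The check has three parts.

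**1. What each arm receives**

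| Component | Intervention | Control as delivered | Control as named in the objective |
|---|---|---|---|
| Routine care | yes | yes | yes |
| Wrist tracker, 14 weeks | yes | yes | not mentioned |
| Weekly activity summary | yes | yes | not mentioned |
| Exergaming | yes | no | no |

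The first two columns differ by exergaming alone, so the arms are not confounded by the tracker. The last two columns differ, so the comparator named is not the one delivered.

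**2. What this does to the activity difference**

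Let E be the effect of exergaming, F the effect of tracker plus feedback on patients in usual care, and o the share of F that is lost when exergaming is also present. All are in SD units relative to true usual care.

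- Intervention arm: E + F(1 − o)
- Control arm: F
- Trial contrast: E + F(1 − o) − F = E − oF
- Full package against true usual care: E + F(1 − o), which exceeds the trial contrast by exactly F

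The document gives none of E, F or o. With the assumed value E = 0.5, the trial contrast (package against usual care in brackets) is:

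| F (assumed) | o = 0 | o = 0.5 | o = 1 |
|---|---|---|---|
| 0.1 | 0.50 (0.60) | 0.45 (0.55) | 0.40 (0.50) |
| 0.2 | 0.50 (0.70) | 0.40 (0.60) | 0.30 (0.50) |
| 0.3 | 0.50 (0.80) | 0.35 (0.65) | 0.20 (0.50) |

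If F = 0, the contrast equals E and the label makes no numerical difference. If the effects add (o = 0), the contrast still equals E. It falls below E only when F is positive and the effects overlap. It falls below the package effect whenever F is positive.

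The pilot cannot estimate F. Trackers are issued after the baseline interview, so there is no tracker-free accelerometry, and no arm goes without the tracker. The self-report questionnaire has a baseline taken before the tracker, but its change in controls mixes F with every other change over 14 weeks.

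**3. Scale against the pilot's precision**

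The 95% half-width for a mean difference, in SD units, is t(0.975, 2n − 2) × √(2/n).

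- 30 per arm, as planned: 0.52 SD
- 24 per arm, after the allowed 20% attrition (30 × 0.8 = 24): 0.58 SD

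The assumed values of F (0.1 to 0.3 SD) lie inside either interval. The pilot would not reveal the shift, so the wording has to carry the distinction.

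**The case against.** The strongest reply is that both arms get the same device and the same summary, so the difference isolates exergaming, which is the thing under study. That stands: shared exposure is not bias. A reader might infer that the control arm is contaminated and the estimate therefore biased towards zero. The document does not support that, because it shows neither that feedback raises activity in controls nor that its effect overlaps with exergaming.

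A reader might also infer from the participation questions that the plan expects the tracker to change behaviour. It does not say so. It asks neutral questions of everyone, and the answers are useful information on reactivity.

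It can further be said that the tracker is disclosed, that routine treatment only may simply mean without FIT HEART, and that little rests on the contrast: feasibility is the main aim, no hypothesis test is planned, no progression criterion uses the activity difference, and causal claims are already limited. This lowers the weight of the point. It does not remove it, because the objective and the control definition still name a condition that no participant receives, and the reported differences are meant to inform the next trial. Whether that trial would use trackers or feedback is not stated; if it keeps both, the control-arm SDs would suit it, provided that they are labelled correctly.

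Finally, one might wish to withhold the summaries from controls. The arms would then differ by feedback as well as exergaming, and an activity difference could not be attributed to either. Controls would also still wear a tracker with a display, so they would still not be on routine treatment only.

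**Conclusion.** The comparator is wrongly described. What is compared is exergaming plus tracker and feedback against routine treatment plus tracker and feedback. That contrast is not confounded by the tracker, but it does not answer the second objective as worded.

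The size is unknown. The shortfall against the full package versus true usual care equals F, whatever F is. The shortfall against the effect of exergaming itself is oF, which is zero if the effects add. The figures of 0.1 to 0.3 SD are assumptions chosen to show the range, not estimates from the document. The point concerns what may be concluded and carried forward; it does not make the pilot's feasibility results unsound.

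**What to change.** Name the comparator as *routine treatment plus activity tracker with weekly feedback* in the abstract's Methods, Study aims and objectives, Routine treatment, and Potential effectiveness of intervention. As the article is published, carry the same wording into the statistical analysis plan, which is still to be agreed before analysis, and into the results report.

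Limit conclusions from the mean differences and confidence intervals to exergaming added to that comparator, and attach the same label to any control-arm changes and SDs used in planning the randomised trial.

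Add reactivity to the tracker and feedback to the limitations, and report by arm the answers on sitting less, changed routine and usefulness of the weekly information, so that reactivity is at least described.

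Leave the feedback procedure equal in both arms. Recruitment restarted in June 2020 and is expected to end in December 2022, so a change now would also split the control group into patients with and without summaries.

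The cost is a few sentences and one descriptive table, with no new data and no change to procedures.
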